##### Mathematical model

This method estimates food volume using a mathematical model/equation. This model relies on the measurements (height and diameter/width) of serveware (i.e., cups, bowls, plates, basins etc.) and cookware (i.e., pot and pans) used in the household, as a reference scale. To obtain the reference scale, field staff in the 2 countries will arrange to visit the households to measure and record the height and width of the serveware household members use to eat. Image captured by a wearable device at the beginning and end of an eating episode will be used to estimate the volume of food consumed using the formula: 
(1)}{}$$\begin{eqnarray*}
V = \frac{{\pi kl{d^2}h}}{4}
\end{eqnarray*}
$$where *V* represents the estimated volume, *k* is the shape parameter, *l* is the level parameter, *d* is the diameter/width of the serveware, and *h* is the height of the serveware. The shape parameter (*k*) can be obtained using 2 methods. In the first method (the precise method), the serveware (e.g., a bowl) is filled with water to its brim to measure and record (in grams) the net weight of water the serveware contains. The parameter *k* is then obtained by dividing the net weight of water [which has the same value in grams as the volume in milliliters (i.e., 1 g ≡ 1 mL)] in the serveware by the calculated volume (also in milliliters) of a hypothetical cylinder having the same diameter and height as the serveware. In the second, which is the approximate method, *k* is selected empirically from a range between 0.5 and 0.8, depending the shape of the serveware. The level parameter (*l*), which represents the fill level of bowl or cup, is visually estimated from the captured image. In this method, *l* must be chosen under the condition 0 < *l* ≤ 1, where 0 and 1, respectively, correspond to “completely empty” and “completely full.”

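### The approximate shape parameter (0.5 to 0.8) has no value for a straight-sided or nearly straight-sided cup, so where it is used for one the volume is understated

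*Protocol article*

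**What the plan says.** The Mathematical model section of the protocol article (under Methods, Portion size estimation) gives V = π·k·l·d²·h/4, where d and h are the vessel's diameter or width and its height, l is the fill level and k the shape parameter. The level is read by eye from the image and must lie above 0 and at most at 1.

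The model is said to rely on measurements of "serveware (i.e., cups, bowls, plates, basins etc.) and cookware (i.e., pot and pans) used in the household". Field staff will visit to "measure and record the height and width of the serveware household members use to eat". The formula is then applied to images from the start and end of an eating episode.

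Two ways of obtaining k are offered:

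- **Precise method.** The vessel "is filled with water to its brim to measure and record (in grams) the net weight of water the serveware contains", and k is that amount divided by the "volume (also in milliliters) of a hypothetical cylinder having the same diameter and height as the serveware".
- **Approximate method.** k "is selected empirically from a range between 0.5 and 0.8, depending the shape of the serveware".

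The section does not say which vessels get which method. It does not confine the approximate method to particular shapes, and it does not say whether inner or outer dimensions are measured.

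**The concern.** The definition of k and the permitted range do not fit together for one ordinary class of vessel. If k is capacity relative to a cylinder of the same diameter and height, a cylinder has k = 1 and a slightly tapered cup has k a little below 1. A range that stops at 0.8 contains neither.

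V is proportional to k, so a capped k passes in full into the estimated volume, always downward. The error belongs to the vessel, so repeat recording days with the same cup do not average it out. The level parameter cannot compensate for a full vessel, because it may not exceed 1. The predictors of accuracy named in the Analytical plan (demography, education, urban or rural, child or adult) do not mention vessel type or the source of k. A shortfall caused by k could therefore be read as a shortfall of the camera method.

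**Working it through.** **Inputs from the Mathematical model section:** V = π·k·l·d²·h/4; k = water capacity / (π·d²·h/4); approximate k from 0.5 to 0.8; l at most 1. The article gives no derivation of 0.5 to 0.8, so the range itself cannot be reproduced. It can only be compared with the k of known shapes.

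**Assumptions:** vessel shapes are mine, since the article describes none. Dimensions are inner dimensions. For tapered cups, l is taken as a share of capacity, or equivalently the cup is emptied from full. A part-full tapered cup with l read as a height fraction has a separate error that is not counted here.

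**Step 1: k by shape.**
- Cylinder: (π·d²·h/4) / (π·d²·h/4) = 1.
- Hemisphere: 2/3. Paraboloid: 0.5.
- Tapered cup with base/rim diameter ratio r: capacity is π·h·d²·(1 + r + r²)/12, so k = (1 + r + r²)/3.

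The range thus suits rounded and clearly tapered vessels: k = 0.5 to 0.8 corresponds to r of about 0.37 to 0.78.

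**Step 2: error in the amount consumed.** Consumed volume is (π·d²·h/4)·k·(l_start − l_end). k factors out, so the relative error is k_used/k_true − 1.

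**Step 3: exact cylinder (k_true = 1).**
- k = 0.8: 0.8/1 − 1 = −20%.
- k = 0.65: 0.65/1 − 1 = −35%.
- k = 0.5: 0.5/1 − 1 = −50%.

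**Step 4: tapered cup with the most favourable permitted k.**

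| Base/rim r | k_true | Best possible error |
|---|---|---|
| 0.70 | 0.730 | 0% |
| 0.80 | 0.813 | −1.6% |
| 0.85 | 0.857 | −6.7% |
| 0.90 | 0.903 | −11.4% |
| 0.95 | 0.951 | −15.9% |
| 1.00 | 1.000 | −20.0% |

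For r = 0.90: (1 + 0.90 + 0.81)/3 = 0.903, and 0.8/0.903 − 1 = −11.4%.

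**Step 5: where the cap starts to bind.** Solving (1 + r + r²)/3 = 0.8 gives r = 0.785, so no understatement is forced below about 78%. The best possible error passes −10% when k_true = 0.8/0.9 = 0.889, that is at r = 0.884.

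**Step 6: same cylinder by water fill.** k = 1, error 0%.

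**The case against.** The strongest reply is that the remedy already stands beside the problem. The water-fill method has no upper limit and returns 1 for a cylinder, and the article never says that the approximate method will be used for a straight-sided cup. Deciding which vessel gets which method could belong in a full field manual. This stands in part: the bias is conditional on the approximate method being chosen. It does not remove the point, because the range is a stated numerical rule, offered without restriction on shape, and it is wrong for near-cylindrical cups whenever it is applied to them.

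Several stronger readings are tempting, and the article does not support them:

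- **That household cups in general lose at least 20%.** No vessel is described as straight-sided. The 20% floor holds only for an exact cylinder, and for many tapered cups the range is adequate.
- **That the contents of pots and pans are understated.** Cookware is listed as a reference scale, but the formula is applied to eating-episode images and the planned measurements are of vessels used to eat. No stated step computes intake from a pot.
- **That the error breaches the ±10% accuracy criterion.** That criterion in the Analytical plan concerns nutrient intake against the weighed record, not the volume in one vessel. This model is also one of three portion-size approaches.
- **That measuring outer dimensions makes matters worse.** For a cylinder it works the other way. With outer size 10 × 10 cm and 2 mm walls and base (an assumption), effective k is (9.6/10)² × (9.8/10) = 0.903, so the best possible error is −11.4% instead of −20%. This is why the figures above are stated for inner dimensions.

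Finally, the planned Bland–Altman analysis and paired t tests against weighed records would show an overall bias. That is true, and the validation is not invalidated, but those analyses would not by themselves say that k was the source.

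**Conclusion.** The point holds in conditional form. By the article's own definition k is 1 for a straight-sided round vessel, and the approximate range excludes that value without excluding such vessels. If the approximate method is used for them, volume is understated by 20% to 50% for an exact cylinder and by at least 11% for a cup whose base is 90% of its rim. These figures rest on inner dimensions, on assumed shapes and, for tapered cups, on level read as a share of capacity. How many study vessels are affected cannot be told from the article. This is an avoidable source of bias in one of the portion-size methods and should be corrected. It is not a flaw in the validation design.

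**What to change.** - Make the water-fill k the default for every vessel that an index case eats or drinks from, done at the visit where height and width are measured. The same d and h enter both k and the volume formula, so with a water-fill k the choice of inner or outer dimensions cancels out.
- Keep the approximate method as a fallback for vessels that cannot be filled. Extend its upper limit to 1.0, or tie k to shape: straight-sided 1.0; tapered (1 + r + r²)/3, with r the base/rim ratio. State that inner dimensions are used.
- Record for each vessel which method supplied k, so that an error from this source can be recognised in the analysis.

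The cost is one water weighing per vessel on a visit already planned, and a sentence or two of text. The downside is a slightly longer visit.

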##### Visual estimation

This method relies on a trained eye to estimate visually the quantity of food on images. To do this accurately, the assessor should be familiar with the local foods as well as having knowledge of the use of aids for portion size estimation. In this study, dedicated local staff in Ghana and Uganda will be trained to perform the visual portion size estimation. Training will consist of: *1*) learning the method of estimation; *2*) practicing the estimation on a standard practice deck of images with known portion sizes of food; and *3*) testing on a selection of images not included in the practice deck. Each assessor will be retested every 3–6 mo to track consistency and accuracy, and additional practice will be conducted if needed before retesting.

Food images for each eating occasion will be viewed using custom software, the AIM software (**Figure 3**). The portion size for each food will be estimated from images captured at the beginning and end of each eating occasion. However, all images for each entire eating occasion will be viewed to determine if additional portions of food were added to or subtracted from the plate or bowl before the end of the eating occasion, and if so the portion size of the additions and subtractions will also be estimated and taken into account to compute total consumption. An example of an addition would be a person taking a second helping; an example of a subtraction would be a person sharing the food on their plate with another person (e.g., a mother feeding a toddler from a common plate). A combination of portion size aids and comparison of food with common reference objects will be used to estimate portion sizes. The reference objects will include serveware (plates, bowls, cups, eating utensils, etc.) and hands/fingers appearing in images next to the foods and beverages. Foods not directly estimated in grams or kilograms will be estimated in volume (e.g., milliliters) and converted to grams using an estimated density (grams per milliliter) from INFOODS (International Network of Food Data Systems) (26, 27) and other sources such as USDA Food Composition Databases.

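### The serveware volume model is correct for tapering vessels only if fill level means a fraction of volume, which is not stated; separately, the approximate k range understates vertical-walled round cups and pots

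*Protocol article*

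**What the plan says.** The Mathematical model section (Protocol article, Methods, Portion size estimation) gives V = πkld²h/4, where d and h are the diameter or width and the height of the vessel, k is a shape parameter and l a level parameter. The vessels named are serveware ("cups, bowls, plates, basins etc") and cookware (pots and pans).

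- **k, precise method.** The vessel is filled to the brim with water, and the water volume is divided by the volume "of a hypothetical cylinder having the same diameter and height as the serveware". No range is given.
- **k, approximate method.** k "is selected empirically from a range between 0.5 and 0.8, depending the shape of the serveware".
- **l.** This is the parameter "which represents the fill level of bowl or cup, is visually estimated from the captured image". It must satisfy 0 < l ≤ 1, "where 0 and 1, respectively, correspond to" an entirely empty and an entirely full vessel. The section does not say whether the scale between these ends is one of height or of volume.
- **Use.** Images "at the beginning and end of an eating episode will be used to estimate the volume of food consumed".

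The model stands beside visual and computational estimation as one of three ways to obtain portion size.

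**The concern.** k adjusts only the full vessel. Nothing in the formula adjusts a part-filled one for shape. An assessor asked to judge a fill level from a photograph will probably score how high the food stands. In a bowl that narrows towards the base, half the height holds less than half the volume, so multiplying the full volume by that score overstates what is in the bowl. The error depends on vessel shape and on start and end levels, so it is systematic for a household that uses the same bowls in the same way.

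The second matter does not depend on how l is read. The stated definition of k gives a value of 1 for a cylinder, and cups and pots are often close to cylinders. An assessor who follows the approximate method cannot choose that value.

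Portion volume feeds directly into the nutrient estimates that the Analytical plan compares with weighed food records. A shape error here would appear there as a method error, although it comes from an undefined parameter and a range set too low.

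**Working it through.** **Inputs.** The formula, both definitions of k, the range 0.5–0.8, and the description and scale of l come from the Mathematical model section. The article gives no worked volume, so there is no figure to reproduce. It gives no vessel shapes either, so those below are assumptions. d and h are taken as inside dimensions.

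**Step 1: reduce the formula.** With k = V_full / (πd²h/4), V = k × l × πd²h/4 = l × V_full. At l = 1 it is exact for every shape.

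**Step 2: l as a fraction of volume.** The true content is l × V_full by definition. The error is 0 for every shape and level.

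**Step 3: l as a fraction of height.** The true content is f(l) × V_full, and the relative error is l/f(l) − 1.

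- Truncated cone, base/top radius ratio r: k = (1 + r + r²)/3. With a = r + (1 − r)l, f(l) = l(r² + ra + a²)/(1 + r + r²). k = 0.5 needs r = 0.366; k = 0.8 needs r = 0.785.
- Curved bowl with a power profile: f(l) = l^(1/k).
- Hemisphere: k = 2/3, f(l) = (3l² − l³)/2.
- Vertical-walled round vessel: k = 1, f(l) = l.

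Example, power profile with k = 0.5 at half height: f = 0.5² = 0.25, so the error is 0.5/0.25 − 1 = +100%.

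Error in the volume present:

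| Shape | f(0.5) | l = 0.5 | l = 0.75 | l = 0.9 |
|---|---|---|---|---|
| Cone, k = 0.5 | 0.2835 | +76.4% | +30.4% | +10.8% |
| Power, k = 0.5 | 0.2500 | +100.0% | +33.3% | +11.1% |
| Hemisphere, k = 2/3 | 0.3125 | +60.0% | +18.5% | +5.8% |
| Cone, k = 0.8 | 0.4399 | +13.7% | +6.5% | +2.5% |
| Power, k = 0.8 | 0.4204 | +18.9% | +7.5% | +2.7% |
| Vertical wall, k = 1 | 0.5000 | 0% | 0% | 0% |

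The error in a single volume passes 10% below about l = 0.91 (k = 0.5), 0.84 (hemisphere) and 0.63–0.68 (k = 0.8).

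**Step 4: volume eaten, still with l as height.** The error is (l₁ − l₂)/(f(l₁) − f(l₂)) − 1, where l₁ is the start level and l₂ the end level.

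| Start to end | Cone 0.5 | Power 0.5 | Hemisphere | Cone 0.8 | Power 0.8 |
|---|---|---|---|---|---|
| 1 to 0 | 0% | 0% | 0% | 0% | 0% |
| 1 to 0.5 | −30.2% | −33.3% | −27.3% | −10.7% | −13.7% |
| 0.75 to 0 | +30.4% | +33.3% | +18.5% | +6.5% | +7.5% |
| 0.5 to 0 | +76.4% | +100.0% | +60.0% | +13.7% | +18.9% |
| 0.9 to 0.1 | +2.5% | 0.0% | −4.3% | +0.2% | −2.5% |

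**Step 5: the approximate k range.** A vertical-walled round vessel has k = 1. The largest value allowed is 0.8, so V is at most 0.8/1 = 80% of the truth, an understatement of at least 20%. At the lower end, 0.5/1 gives 50%. For such a vessel height fraction and volume fraction coincide, and the formula is linear in k. The shortfall is therefore the same at any fill, for volume present and for volume eaten, under either reading of l.

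**The case against.** The strongest reply is that l is never called a height. Its two ends fit a volume fraction equally well, and on that reading the formula is exact for every shape. A journal article may also leave the working definition of l to assessor instructions. The first part stands: the article does not state a wrong formula, but one that is right under only one reading. The second part stands less well, because the words chosen, fill level, point the assessor towards the other reading.

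Several stronger claims are tempting, and the document does not support them:

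- **That the model rules out cylinders.** The range 0.5–0.8 binds only the approximate method. The water-fill method has no cap and returns k near 1 for a cylinder.
- **That linearity in l requires k = 1.** What matters is vertical walls. A truncated cone has straight sides and still fails. A vertical-walled oval dish whose width is taken along its long axis can have k below 1, and the formula is exact for it.
- **That intake is biased in one direction, or beyond the ±10% limit.** The sign changes with start and end levels, and a brim-full vessel that is emptied gives no error. The ±10% criterion concerns nutrient intake, not the volume in one vessel.
- **That all portion sizes are biased.** This is one of three methods, and the passive method is itself tested against weighed records.
- **That second helpings are lost.** For the visual method, "all images for each entire eating occasion will be viewed to determine if additional portions of food were added to or subtracted"; the Mathematical model section says nothing on this. Silence in a condensed article is not exclusion.
- **That an emptied bowl cannot be handled.** The strict inequality at 0 is a slip of notation, since the same sentence defines 0 as empty.

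**Conclusion.** Two points hold.

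First, l is not adequately defined. The model is exact if l is the filled fraction of volume. If l is scored as a height, a half-high fill in a round tapering vessel is overstated by about 14% (k = 0.8, cone) to 100% (k = 0.5, power profile). Volume eaten then ranges from 11–33% too low when a full vessel is half eaten to 14–100% too high when a half-high one is emptied. It is correct from brim-full to empty. These sizes rest on the assumed shapes and on assessors judging height.

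Second, whichever reading of l is meant, the approximate k range understates vertical-walled round cups and pots by at least 20% at any fill, taking k = 1 and inside dimensions. This follows from the article's own definition of k. Vessels measured with water are not affected.

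Both conclusions are confined to volumes obtained with this model; the second applies only where k is chosen by the approximate method.

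**What to change.** 1. Define l as the filled fraction of the vessel's volume, and train assessors to judge that, with practice images of known volume. The formula then stays as it is.
2. If l is meant as a height fraction, replace l by a shape-specific function f(l). The form l^(1/k) is only an approximation. For a truncated cone with base/top ratio 0.5 (k = 0.58) at half height it gives 0.305 against a true 0.339, about 10% low, where linear l is 47% high. It must not be used if l is a volume fraction, because it would put bias into a correct formula.
3. Extend the approximate k range to 1.0.
4. Write 0 ≤ l ≤ 1, so that an emptied vessel is allowed.

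Items 1, 3 and 4 cost minor rewording and some assessor training, with no new household measurements. Item 2 would cost more if f(l) is to come from a fill-height table, since the water-filling step would need readings at intermediate levels.

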##### Computational estimation

In this method, a combination of ellipse extraction algorithm, deep learning, and AI will be used to estimate food volume in different serveware such as bowls, cups, basins, and plates.

Generally, in imaging, the circular edge of serveware such as bowls and cups appears elliptical on images because the lens of a wearable camera is usually at a certain angle (∼40°) to the top edge of the serveware. In this study, we will use a custom-made ellipse extraction algorithm to carefully extract the elliptical outline of serveware on the images, overcoming a number of challenges; these include partial obscuring of the elliptical outline by food, and multiple ellipses due to circular food patterns or printed decorations on the serveware. When the desired elliptical outline of the serveware is extracted, the eccentricity of the ellipse, the measured diameter of the container, and several parameters of the camera (called intrinsic parameters) are utilized to construct a coordinate transformation from the image pixel coordinates to the real-world coordinates. This transformation is a key step in enabling food volume estimation in a metric unit (e.g., milliliters) (28, 29).

For foods served on plates, we have previously explored the use of fitting a computer-generated net cover (wireframes) of preselected shapes (e.g., a sphere or a wedge) to the food in an image to aid in the estimation of food volume (30). Although successful, this manual process is time consuming and unsuitable for a large-scale study. In addition, the wireframe method is imprecise when the food shape is highly irregular, which is common with semisolid, amorphous foods. For the proposed study, we have developed an advanced method using an AI technology. Standard volumetric reference measures such as a cup, a golf ball, a fist, a deck of cards, and so forth were used to train the AI system to estimate the volume of food on images, akin to how a human is trained to conduct visual portion size estimation. The CNN in the AI system takes the food images as the input and a set of probabilities with respect to the standard volumetric references is produced as output, and the probability values are then combined to yield the estimated food volume. Preliminary testing of the AI system in a laboratory setting across 630 food images of known volume produced an average relative error of 11.5% ([name], [name], [name], unpublished results, 2019). This system will be further enhanced and used in the proposed study.

#### Assessment of nutritional content

Nutritional content of foods captured on the images will be assessed using the AIM software as the interface (Figure 3). The AIM software is capable of incorporating different food composition databases, such as the West African Foods database (31), Kenyan Food database (32), UK Integrated Food Composition dataset (33), and the USDA Food Composition databases (34), allowing users to choose from databases. In addition, the AIM software also accepts ad hoc databases, for example, in situations where “back of pack” nutrient data of food brands need to be added. The closest match for foods in this study will be selected, preferentially the West African Foods database for Ghanaian foods and the East African Food database for Ugandan foods. When required these selections will be supported by other food composition databases, such as the USDA and UK databases. The nutrition analysis for each person's daily food intake will be saved and exported to an Excel (Microsoft) file for analysis.

